## Abstract

**Background:**

Nonprofessional caregivers are highly important in the everyday life of patients with depression. Yet, they may experience increased levels of burden, stress, depression, and anxiety. Therefore, there is a need for interventions that relieve symptoms and are accessible and time-efficient. This paper describes the protocol of a pilot study to evaluate (1) the feasibility of an online self-management intervention, E-care 4 caregivers, for the nonprofessional caregiver of patients with depression, and (2) the initial effects of E-care 4 caregivers on psychological distress, subjective burden, symptoms of anxiety and depression, and quality of life.

**Methods/design:**

The study is a randomized controlled trial in which we are comparing the E-care 4 caregivers online intervention with a wait list control group. Eighty-four nonprofessional caregivers of patients with depression aged 18 years or older are being recruited from among the general population. Feasibility is determined by semistructured telephone interviews evaluating the subjects’ satisfaction with the intervention and by using a questionnaire on the user-friendliness of the system. The primary outcome measure used to examine the initial effects of the intervention is psychological distress. Secondary outcome measures are subjective burden, symptoms of anxiety and depression, level of mastery, and quality of life. Assessments will be done at baseline and 6 weeks later. Statistical analysis of the effects of the intervention will be carried out on the basis of the intention-to-treat principle.

**Discussion:**

E-care 4 caregivers could potentially benefit nonprofessional caregivers, as well as patients and professionals indirectly.

**Trial registration:**

Netherlands Trial Register identifier: NTR5268. Registered on 30 June 2015.

## Background

Nonprofessional caregivers are of high importance in the everyday lives of patients with depression. They may contribute significantly to day-to-day personal care and psychological support. The importance of nonprofessional caregivers has been recognized by the Dutch government, which encourages a greater role for caregivers in providing psychological support [1], as the care for these patients is virtually unattainable by professional health care providers alone. However, caring for a loved one with depression also has drawbacks, such as the risk of overburden due to decreased time for personal activities, disrupted everyday life [2], communication problems, financial difficulties, and social exclusion [3, 4]. This puts these nonprofessional caregivers at risk for developing symptoms of stress, anxiety, and depression, which often are associated with reduced quality of life [4–8]. Research by de Boer and colleagues [5] showed that 80 % of nonprofessional caregivers express a need for more support in the form of information, advice, or guidance.

Prevention research has demonstrated that early intervention is effective in preventing overburdening and decreasing distress. Stam and Cuijpers [9], for example, have demonstrated that a group psychoeducational intervention can reduce the experienced burden of nonprofessional caregivers of patients with a range of psychological problems. Likewise, a group psychoeducational intervention for nonprofessional caregivers caring for a patient with bipolar disorder, as compared with a control group, also demonstrated a reduction in experienced burden as well as an increase in knowledge about the disorder [10]. However, these group interventions are time-consuming and often do not fit into a caregiver’s busy schedule.

An online self-management intervention for the nonprofessional caregiver of a patient with depression that is aimed at increasing mental resilience and self-reliance to reduce subjective burden and prevent the development of psychological symptoms may overcome these barriers. It could be accessed 24 h per day, 7 days per week at a location and within a time frame that are the most convenient for the caregiver. Such an intervention would also be relatively easy to implement on a larger scale in the general population with minimal costs.

Previous research demonstrated robust evidence that Internet-based treatments can be effective for reducing symptoms of depression and anxiety [11, 12]. The effect sizes are comparable to those observed in face-to-face treatment [13]. However, Internet-based interventions have the potential to be more cost-effective than face-to-face treatment [14]. Also, an online intervention that was developed for nonprofessional caregivers caring for people with dementia was well-received (www.dementieonline.nl). One study showed positive results of web-based peer support for families of patients with depression, although the researchers in that study recommended including professional feedback as well [15]. However, to date, no study has examined the effects of online interventions based on cognitive behavioral therapy (CBT) principles for caregivers of patients with depression [16].

This paper describes the protocol of a pilot study designed to evaluate (1) the feasibility of an online self-management intervention, E-care 4 caregivers, for nonprofessional caregivers of patients with depression, and (2) the initial effects of E-care 4 caregivers on psychological distress, subjective burden, symptoms of anxiety and depression, level of mastery, and quality of life.

## Methods/design

This study is a two-arm randomized controlled trial (RCT) comparing the online intervention E-care 4 caregivers with a wait list control group (WLC). Assessments will be done at baseline and 6 weeks later.

### Procedure

Nonprofessional caregivers will be recruited via the Dutch Depression Association and by advertisements on the Internet and other media (see Figure 1). Caregivers who are interested in taking part can find more information about the study on the website of the Mental Health Fund (Fonds Psychische Gezondheid), which hosts the study website. If they are interested in taking part in the study, they can register via the website. Next, they have to provide digital informed consent before being directed to the online baseline assessment. Those who are eligible to take part will be randomized to the intervention condition or the WLC group. Subjects in the intervention condition will have access to the online intervention for 6 weeks, while those assigned to the WLC condition will get access to the E-care 4 caregivers intervention after the 6-week assessment. Participants in both arms will be invited to complete an online assessment 6 weeks after baseline. Participants in the E-care 4 caregivers intervention group may also be approached for a qualitative interview. The Consolidated Standards of Reporting Trials (CONSORT) will be followed for reporting the trial [17]. Participants who complete all data entry points will receive an incentive of 25 euros.

**Fig. 1 Fig1:**
[figure not shown]
Flow diagram of the trial. *K10* Kessler Psychological Distress Scale

### Study population

This study targets adult nonprofessional caregivers of loved ones with depression (partners, parents, children, siblings, family, or friends). Included are (self-reported) nonprofessional caregivers aged 18 years and older who care for a loved one with depression (including those with comorbid disorders). Excluded are nonprofessional caregivers without Internet access and those with no proficiency in Dutch.

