### Randomization and blinding

All participants eligible to take part will be randomized to the E-care 4 caregivers intervention or the WLC group, stratified by their scores on the K10 using a cutoff score of 20 [19]. The random allocation sequence and the randomization process will be performed by an independent researcher in the Random Allocation Software program. Due to the nature of the intervention, double-blinding of group allocation is not possible.

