### Intervention: E-care 4 caregivers

The online self-management course comprises eight modules. The elements of it are described in Table 1. The modules include theory, exercises, examples of caregivers` experiences, and short videos. This intervention will include personalized feedback provided by a coach and a diary app. An Internet forum that is developed as a closed group on Facebook will also be a part of the online course. This forum is used for peer contact and is moderated by a coach.

**Table 1 Tab1:** Content online intervention

Themes	Topics	Goals
1. What is depression?	Psychoeducation concerning symptoms, diagnosis, types, and causes of, as well as treatment options for, depression	To familiarize caregivers with the nature of the depressive disorder and its treatment to enable recognition of symptoms
2. Implications of depression for the caregiver	Emotions that can arise for the caregiver and the family, grief processes that occur, and practical implications of the depression	To recognize, validate, and accept negative emotions that can arise in a caregiver when facing the situation that a loved one has depression
3. How to think differently	Automatic thoughts, cognitive distortions, and how to correct these using principles of cognitive therapy	Using cognitive principles to recognize dysfunctional thoughts and change them to help caregivers in this stressful situation
4. Signaling stress and burnout	Psychoeducation about causes and signs of stress using the capabilities/workload model	Recognition and/or prevention of symptoms of overburdening and stress
5. Caring for yourself	Tips to better take care of yourself and your own boundaries with exercises about help-seeking, assertiveness, time-management, and relaxation exercises	Preventing and/or decreasing symptoms of overburdening and stress via various exercises
6. Learning to communicate better	Psychoeducation about communicating with someone with depression using the disarm technique and principles of emotionally focused therapy	To recognize your own role in communicating while understanding someone with depression better to avoid constant repetitive arguments
7. Coping with suicidality	Psychoeducation about suicidality, tips to communicate about suicidality, establishing and following safety procedures	Empowering caregiver with more knowledge about suicidality and safety measures as well as gaining more confidence in communication and setting boundaries

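### Caregivers of the same depressed person can be enrolled and randomised separately, so a wait-listed co-caregiver can be exposed to the course; a one-per-patient rule would prevent this

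*Protocol article*

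**What the plan says.** All references are to the protocol article.

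- **Study population.** Eligibility is defined per caregiver: "Included are (self-reported) nonprofessional caregivers aged 18 years and older who care for a loved one with depression". The target group covers every kind of relative as well as friends: "adult nonprofessional caregivers of loved ones with depression (partners, parents, children, siblings, family, or friends". The stated exclusions are these: "Excluded are nonprofessional caregivers without Internet access and those with no proficiency in Dutch".
- **Procedure.** Recruitment runs through a patient association and public advertising, and people enrol themselves: "If they are interested in taking part in the study, they can register via the website". The control is a wait list: "those assigned to the WLC condition will get access to the E-care 4 caregivers intervention after the 6-week assessment".
- **Randomization and blinding.** The unit is the individual participant: "All participants eligible to take part will be randomized to the E-care 4 caregivers intervention or the WLC group". The only stratification factor is the K10 score, dichotomised at 20, and no household or family factor is named.
- **Intervention: E-care 4 caregivers.** "The modules include theory, exercises, examples of caregivers` experiences, and short videos". The course also has individual coach feedback, a diary app and a closed, moderated forum.
- **Other questions.** Characteristics of the cared-for person are collected at baseline, but no use of them to link caregivers is described.
- **Statistical analysis.** Repeated measures analysis of variance, with sensitivity analyses on K10.

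**The concern.** Applied as written, these rules let both parents of one patient, or a partner and an adult child, enter as separate participants and be allocated independently.

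The contrast with a wait list depends on controls not receiving the course for six weeks. Text, exercises and videos are easy to show to someone at home. Some modules (communication, suicidality, children of the patient) concern a situation that both caregivers share. If one of them deals with the patient differently, the other's burden can change without any material being passed on.

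What is at stake is some dilution of the arm difference in psychological distress and burden. The Discussion intends the pilot to inform the sample size of a later effectiveness trial, so any dilution of the observed effect could carry over into that calculation.

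**Working it through.** **The plan's own figure.** The Sample size section takes 70 participants and allows for 20% attrition: 70 × 1.20 = 84, as stated. How that allowance is applied does not bear on this point.

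**Inputs**

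- N = 84, from the Sample size section.
- Arms of 42 and 42. This is an assumption, since the article states no allocation ratio.
- *s*, the share of participants who share a patient with one other participant. It is not given, so it is assumed to be 5%, 10% or 20%.
- *c*, the fraction of the course's effect that reaches a wait-listed co-caregiver. It is not given, so it is assumed to lie between 25% and 100%.

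**Step 1: chance that a pair is split.** Once one member is placed, 42 of the remaining 83 places are in the other arm: 42/83 = 0.506.

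**Step 2: controls with a co-caregiver in the intervention arm.** Pairs = 84*s*/2. Expected split pairs = pairs × 0.506. Share of controls = split pairs/42, which reduces to 0.506*s*.

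**Step 3: shrinkage of the arm difference.** Assuming that what passes across is some or all of the benefit, the observed difference = true difference × (1 − *c* × share of controls).

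| *s* | Pairs | Expected split pairs | Share of controls | Shrinkage, *c* = 25% | Shrinkage, *c* = 100% |
|---|---|---|---|---|---|
| 5% | 2.1 | 1.06 | 2.5% | 0.6% | 2.5% |
| 10% | 4.2 | 2.13 | 5.1% | 1.3% | 5.1% |
| 20% | 8.4 | 4.25 | 10.1% | 2.5% | 10.1% |

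**Step 4: comparison with the pilot's precision.** With 35 per arm (70/2), the unadjusted 95% confidence half-width for a standardised difference is about 1.96 × √(2/35) = 0.47. For an assumed true difference of 0.3 to 0.5, a 10% shrinkage is 0.03 to 0.05, or about 6 to 11% of that half-width.

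**Step 5: consequence for a later trial.** If the observed effect were used for planning, required n would scale as 1/effect². A shrinkage of 2.5% gives 1/0.975² = 1.05, and 10% gives 1/0.90² = 1.23. The later trial would be planned about 5 to 23% too large at full transfer, and less at partial transfer.

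**Step 6: standard errors.** Let ρ be the correlation within a pair, S the number of same-arm pairs and D the number of split pairs. Then the variance of the difference in means = (2σ²/42) × [1 + ρ(S − D)/42]. With 8 pairs, expected S = 8 × 41/83 = 3.95 and expected D = 8 × 42/83 = 4.05. At ρ = 0.5 the bracket is 1 − 0.5 × 0.10/42 = 0.999. Same-arm and split pairs cancel on average.

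**The case against.** The strongest reply is that this argues from silence in a condensed article. Eligibility takes a few sentences, registration checks are often left to a fuller document, and the flow diagram is not shown. That limits the claim, because a rule stated elsewhere cannot be excluded. It does not remove the claim: the article gives its eligibility criteria and its randomisation rule, and those rules as stated admit co-caregivers and allocate them one by one.

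The second reply concerns size, and much of it stands. No co-enrolment rate is documented, and recruitment is not through families. The Content section puts the focus on the caregiver rather than the patient. Coach feedback and the closed forum do not pass easily to someone else, so full transfer is an upper bound. Password protection, named under Prerequisites, restricts log-in, though not sharing at home. The study is a pilot and claims only preliminary conclusions on effectiveness.

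A reader might also infer four stronger things, which the document does not support:

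- **That the control arm is in fact exposed.** Neither co-enrolment nor sharing is shown, only that nothing stated prevents them.
- **That correlated pairs make the standard errors materially wrong.** Under individual randomisation the effects largely cancel (Step 6).
- **That pairs could not be found afterwards.** The baseline data on the cared-for person (age, sex, diagnosis, living situation and more) could allow approximate matching, although none is planned.
- **That wait-listed people would have relatives register to gain earlier access.** This is speculation, and the wait is six weeks.

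**Conclusion.** The point holds as a foreseeable and avoidable dilution, not as a demonstrated bias. The stated rules let several caregivers of one patient be randomised separately, and about half of any such pairs (51%) would be split.

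If 5 to 20% of the 84 participants share a patient, about 2.5 to 10% of controls would have a co-caregiver in the intervention arm. The arm difference would then shrink by at most 2.5 to 10%, toward no difference, and by less with partial transfer.

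This rests on an assumed co-enrolment rate, families contributing two participants each, and equal arms. Even the upper figure is small beside the pilot's sampling error. The case for acting is that prevention costs very little.

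**What to change.** Add to the Study population section that one caregiver per depressed person is randomised, namely the first to register. Check this with one question at registration on whether another caregiver of the same person has registered or is taking part. The target of 84 stays as it is.

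Recruitment has already begun (Trial status), so the change goes through the amendment route described under Ethical approval. Put the same question to those already enrolled, flag linked participants, and exclude or account for them in the K10 sensitivity analysis that the Statistical analysis section already foresees.

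The cost is one question, one eligibility line and a few otherwise eligible volunteers, who are lost and replaced by others.

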#### Sample size

There are no definitive guidelines for sample sizes of pilot studies. On the basis of a simulation study [18], a sample size of 70 participants is recommended to estimate pooled standard deviations for a continuous variable. Taking into account an attrition rate of 20 %, we will include 84 respondents in total.

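### Enrolling 84 does not allow for 20% attrition from a target of 70: about 67 would be expected to remain, and the plan's own inputs require 88

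*Protocol article*

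**What the plan says.** The Sample size section contains the whole justification for the trial's size. It first observes that no firm rules exist for sizing a pilot. It then cites a simulation study, on the basis of which "a sample size of 70 participants is recommended to estimate pooled standard deviations for a continuous variable". The next sentence makes the allowance for loss: "Taking into account an attrition rate of 20" per cent, "we will include 84 respondents in total".

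The abstract repeats the result: "Eighty-four nonprofessional caregivers of patients with depression aged 18 years or older are being recruited".

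Two facts about the design matter here. Under Methods/design, the trial has two arms and one follow-up: "Assessments will be done at baseline and 6 weeks later". Attrition therefore means loss between baseline and the 6-week assessment. The article gives no other attrition rate, does not print the inflation formula, and does not say that fewer than 70 remaining would be acceptable.

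**The concern.** An attrition rate is the share of enrolled participants who are lost. To end with a given number, that number must be divided by the share retained. Multiplying it by one plus the attrition rate always gives too few, because the loss applies to the larger enrolled group and not to the target. The figure of 84 looks like the product of that slip.

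What is at stake is whether the stated size meets its stated purpose. The article offers no power calculation; the 70 for the pooled standard deviation is the only benchmark. The Discussion relies on the same purpose when it says that the pilot will reliably inform the size of a later effectiveness trial. If enrolment is expected to fall short of 70 under the plan's own attrition rate, the justification does not support the number.

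**Working it through.** **Inputs**

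| Input | Value | Source |
|---|---|---|
| Target for estimating the pooled SD | 70 in total | Sample size |
| Attrition rate | 20% | Sample size |
| Planned enrolment | 84 in total | Sample size; Abstract |
| Arms | 2 | Methods/design |
| Allocation ratio | not stated; 1:1 assumed for the per-arm check only | assumption |

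**1. Reproducing the plan's figure.** Target × (1 + attrition) = 70 × 1.20 = 84. This matches exactly. Because the formula is not printed, this origin is inferred.

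**2. The inflation that the inputs require.** Target / (1 − attrition) = 70 / 0.80 = 87.5, rounded up to 88. Check: 88 × 0.80 = 70.4, which meets 70 in expectation.

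**3. What 84 delivers at 20% attrition.** 84 × 0.80 = 67.2, about 67. This is about 3 below 70, and enrolment is 88 − 84 = 4 below what step 2 requires.

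**4. The attrition that 84 can absorb.** 1 − 70/84 = 16.7%. No such rate appears in the article.

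**5. Could rounding by arm explain 84?** Assuming 1:1 allocation, 35 per arm are needed at the end.
- 35 / 0.80 = 43.75, rounded up to 44 per arm, 88 in total.
- 35 × 1.20 = 42 per arm, 84 in total.

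Rounding does not turn 88 into 84.

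**6. Chance of ending with at least 70.** Assuming that each participant drops out independently with probability 0.20, the binomial probability that at least 70 remain is about 0.27 with 84 enrolled and about 0.60 with 88.

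**7. Effect on precision.** The approximate relative standard error of a pooled SD from two groups is 1/√(2(n − 2)).
- n = 70: 1/√136 = 8.6%.
- n = 67: 1/√130 = 8.8%.

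**The case against.** The strongest reply concerns importance, since the arithmetic is not open to dispute.

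- **The 70 is a recommendation, not a requirement.** The article itself says that pilot sizing has no settled rules, and no test, power or precision threshold is tied to 70. A move from 8.6% to 8.8% in relative standard error would not materially change the planning of a later trial. This stands, and it limits the practical consequence.
- **Much of the pilot does not depend on the number.** Feasibility, the first aim, rests on the usability scale and on interviews that continue until saturation. The K10 is also measured at baseline in everyone, so a baseline SD can use all 84. This stands too. The shortfall touches the 6-week SD and change scores.
- **The 70 might mean participants enrolled, not retained.** The article does not say which, and the simulation study is not at hand. But if 70 meant enrolled, no allowance for attrition would be needed, and the text makes one. Retained is the only reading under which the step from 70 to 84 has a purpose.
- **Enrolling 88 gives no guarantee either.** This is true: the chance of at least 70 is about 0.60. However, 88 meets the target in expectation, and 84 does not.

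None of these points makes 70, 20% and 84 consistent.

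**Conclusion.** The concern holds. With 20% attrition, 84 enrolled leaves about 67, not 70; the plan's own inputs call for 88. The stated size is 4 too low for its stated basis, and it secures 70 only if attrition does not exceed 16.7%.

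The conclusion assumes that 70 is the number wanted at the end and that 20% is a share of those enrolled. It does not depend on how 84 was obtained, nor on the allocation ratio. The probabilities of 0.27 and 0.60 additionally assume independent dropout.

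The effect on the pilot's usefulness is slight. The reason to correct it is that a wrong figure sits in the sole justification of the trial's size and is carried into the abstract.

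**What to change.** Choose one of two corrections.

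1. **Keep 84 and correct the statement.** Say that at 20% attrition about 67 participants are expected at 6 weeks, and that 70 is reached only if attrition is at most 16.7%. This costs one sentence. The abstract already says 84 and needs no change.
2. **Enrol 88.** State the calculation as 70/0.80 = 87.5, rounded up to 88 (44 per arm if allocation is 1:1), and change the abstract to match. This means four more online participants, at up to 4 × 25 = 100 euros in incentives under the Procedure section. Because recruitment began in September 2015 (Trial status) and protocol changes need a formal amendment approved by the sponsor (Ethical approval), it also carries that administrative step.

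Given the small difference in precision, the first option is sufficient. Neither changes the design, the outcomes or the analysis.
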